#### Transcutaneous oxygen pressure (TcpO_2_)

TcpO_2_ measurements will be performed during the cardiorespiratory tests using sensors that will be non-invasively attached to the skin and allow to heat. The sensors induce skin blood capillary dilatation through heat, which increases the blood flow and results in oxygen diffusion through the skin to the sensor. The sensor measures TcpO_2_ values inwardly through an electrochemical process.

Measurements will be performed using the TINA TCM400 TcpO_2_ device (Radiometer, Copenhagen, Denmark). The temperature of the probe will be set to 44.5 °C to allow maximal skin vasodilation, thereby decreasing the arterial-to-skin surface oxygen pressure gradient. Before the exercise test, 15–20 min will be allowed with the probe attached to the skin for stabilisation of TcpO_2_ value. Following the test, the TcpO_2_ values will be automatically corrected according to a temperature of 37 °C by the TINA device. The electrode will be placed slightly below the right scapula on the back away from any bone.

Fixation rings will be used to hold the probe attached to the skin and this will be filled with two small drops of contact fluid before attachment to the sensor. The fluid will then be heated causing the subsequent dilatation of the skin. The raw values of the patient’s oxygen perfusion will be defined as previously described in Wasilewski et al. [32].

#### Health-related quality of life (HRQoL)

##### EQ-5D-5L questionnaire

The EQ-5D-5L questionnaire will measure the main outcome to assess the patients’ HRQoL throughout the study (baseline, 3- and 6-month follow-up). The EQ-5D-5L is a generic measure of health status, where health is characterised by five dimensions (mobility, self-care, ability to undertake usual activities, pain, anxiety/depression) [19]. Patients will be asked to describe their level of health on each dimension using one of five levels, namely no problems, slight problems, moderate problems, severe problems or extreme problems. To evaluate the EQ-5D-5L outcome in the overall pre- and post-exercise intervention we will calculate the quality-adjusted life years (a metric used in cost-utility analysis that combines length and quality of life in a single parameter; [33]). We will also report digital ulcers, hospitalisation for iloprost infusion and digital amputations.

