To our knowledge, the feasibility of a combined HIIT protocol with short intervals (30 s at 100% peak power output and 30 s passive recovery) and a circuit RT programme on SSc patients has not yet been examined. Moreover, the efficacy of exercise on microcirculation in SSc patients constitutes another unexplored element of SS. Therefore, the primary aim of our study would be to investigate the feasibility of exercise in patients with SSc and the secondary aim is to explore the effects of exercise on microcirculation. Our study objectives are (1) to estimate the rates of recruitment and retention for a future definitive trial of a 12-week supervised exercise programme for SSc patients; (2) to estimate the rates of attendance to and compliance with the supervised exercise programme; (3) to assess the tolerance, acceptability and enjoyment levels of the training protocol; (4) to investigate the effects of exercise on microvascular reactivity in the digital area; (5) to identify and quantify the training dose that may induce microcirculatory improvements in SSc patients; (6) to assess the effects of exercise on HRQoL of SSc patients measured through generic questionnaires and interviews; and (7) to conduct post-intervention interviews with patients to explore individual’s experiences of the study’s procedures and exercise programme.

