### Statistical analysis

The sample size for a feasibility study should be adequate to estimate the critical metrics needed to assess the feasibility of conducting the definitive study, with sufficient precision [34]. The critical metrics are the consent rate (i.e. the proportion of eligible patients who consent to participate and be randomised), improvement in microcirculation and quality of life as well as compliance with treatment, and attrition rates. Fifteen patients in each group (*n* = 30 in total) will provide a sufficiently precise (within 15 percentage points for a 90% confidence interval) estimate of the proportion willing to be randomised, assuming 35–40% intention to be randomised.

The SPSS software (version 23, IBM SPSS, New York, USA) will be used to enter quantitative data and cleaning the data and to carry out missing values imputation and statistical analysis. The descriptive statistics, including mean and standard deviation, will be presented for basic demographics and primary and secondary outcomes of the patients in intervention and control groups. For categorical data, the χ^2^ test will be used to infer on the significant association. Independent and paired samples *t* tests will be used to account for the changes upon the primary and secondary outcomes within the group at pre- and post-exercise intervention but also between the two groups. Kolmogorov–Smirnov and Shapiro–Wilk tests will be used to test the normal distribution of the dependent variable and Levene’s test will be used to test the homogeneity of variances. Pearson’s r will test any relations and interactions between our variables. The qualitative analysis will be performed using framework analysis [35], aiming to describe individuals’ experiences of exercise, searching for common, recurrent patterns but also exploring participant experiences that might explain behaviour and improve advice and services in the future. Data saturation will be achieved when similar themes arise repeatedly and no new themes arise in the interview.

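### Evaluating EQ-5D-5L before and after exercise by QALYs does not fit the visit schedule or the stated t tests: there is no pre-programme QALY, and a single 0–6 month QALY needs baseline adjustment

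*Protocol article*

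**What the plan says.** The EQ-5D-5L questionnaire subsection makes this instrument the main measure of health-related quality of life, collected "throughout the study (baseline, 3- and 6-month follow-up"). It then fixes the summary quantity: "To evaluate the EQ-5D-5L outcome in the overall pre- and post-exercise intervention we will calculate the quality-adjusted life years". The same sentence describes a QALY as "a metric used in cost-utility analysis that combines length and quality of life in a single parameter". That subsection names no per-visit index or visual analogue score as the analysed quantity.

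The Statistical analysis section says that independent and paired t tests "will be used to account for the changes upon the primary and secondary outcomes within the group at pre- and post-exercise intervention", and also between the two groups. It mentions no baseline covariate.

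The outcome has a declared purpose. Objective 6 in the Background is "to assess the effects of exercise on HRQoL of SSc patients measured through generic questionnaires and interviews". The sample-size paragraph counts among its critical metrics "improvement in microcirculation and quality of life as well as compliance with treatment, and attrition rates".

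**The concern.** The article names both a summary measure and a comparison, and the two do not fit together. A before/after comparison needs a value at each time point. A QALY belongs to a stretch of time, as the article's own description (length combined with quality) makes clear. Two readings are possible, and each has its own difficulty:

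- **One QALY before and one after the programme.** The first does not exist, so a paired test has only one member of each pair.
- **One QALY per patient over the six months.** This can be calculated, but it has no before/after change, and part of it is health measured before any exercise. The only stated between-arm test is an unadjusted t test.

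At stake are the answer to objective 6 and the quality-of-life estimate passed to the definitive trial.

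**Working it through.** **Plan's own figure.** The documents give no SD, effect size or power for EQ-5D-5L or QALYs. The only sample-size figure concerns the proportion willing to be randomised. It reproduces: with n = 30 the 90% half-width is 0.143 at 35% and 0.147 at 40%, both within 15 points. It has no bearing on this outcome.

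**Inputs from the article.** EQ-5D-5L at 0, 3 and 6 months, with none before baseline (EQ-5D-5L questionnaire; Baseline measurements); 15 patients per arm (Statistical analysis).

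**Inputs assumed.** Index SD 0.20–0.25; correlation between baseline and follow-up index (ρ) 0.5–0.8; true index gain of 0.08 at both 3 and 6 months.

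**Reading 1: a QALY before and after.** No time elapses at the baseline visit and no earlier assessment exists. The pre-programme QALY is zero or undefined, and a paired test cannot be run on it.

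**Reading 2: one 0–6 month QALY.**

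1. Trapezium rule in years, with u₀, u₃ and u₆ the index at each visit: QALY = 0.125·u₀ + 0.25·u₃ + 0.125·u₆. The weights sum to 0.5, so baseline carries 0.125/0.5 = 25%.
2. SE of the chance baseline difference = SD × √(2/15): 0.073 at SD 0.20 and 0.091 at SD 0.25.
3. Effect of a one-SE imbalance through the baseline weight alone = 0.125 × SE: 0.125 × 0.073 = 0.009; 0.125 × 0.091 = 0.011.
4. Total effect if baseline differences carry into follow-up = SE × (0.125 + 0.375ρ): 0.073 × 0.3125 = 0.023 (SD 0.20, ρ 0.5) up to 0.091 × 0.425 = 0.039 (SD 0.25, ρ 0.8).
5. QALY difference from the assumed true gain = 0.08 × (0.25 + 0.125) = 0.030.

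A one-SE imbalance therefore moves the unadjusted difference by about 30–38% of that gain through the baseline weight alone (0.0091/0.030 to 0.0114/0.030), and by about 76–129% in total (0.0228/0.030 to 0.0388/0.030).

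**Precision.** With SD 0.20 and equal correlation of 0.5, 0.7 or 0.8 between all visits, the QALY has SD 0.083, 0.090 or 0.094, and its correlation with the baseline index is 0.75, 0.86 or 0.91. Adjusting for baseline multiplies the standard error by √(1 − r²), where r is that correlation: 0.66, 0.51 or 0.42. For a difference of 0.030 with 15 per arm, power is about 17%, 15% or 14% unadjusted and 33%, 43% or 56% adjusted.

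**The case against.** The strongest reply is that the article never mentions two QALYs. Its sentence refers to the overall evaluation straight after listing three assessments, which can be read as one QALY per patient over the study. That is the standard construction. The t-test sentence is generic: it covers all primary and secondary outcomes, nominally including recruitment and retention rates, to which no paired test could apply. It is therefore weak evidence of a plan to run a paired test on QALYs. Value set, area-under-the-curve details and covariates are commonly left to an analysis plan. The outcome is secondary in a feasibility trial, and objective 6 also draws on interviews.

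Much of this stands. The two difficulties belong to alternative readings and cannot both apply to one analysis. The silence on baseline adjustment would not be a finding by itself. What survives is narrower: the published sentence ties QALYs to a before/after evaluation that they cannot support, and an analysis plan would have to depart from that wording rather than fill it in. The single-QALY reading removes the undefined quantity, but then the stated analysis of change does not apply, and the only stated comparison left is an unadjusted t test.

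A reader might go further and infer that the quality-of-life result would be biased. The documents do not support that. Allocation is randomised (Study design), so an unadjusted between-arm difference is unbiased on average; the cost is sensitivity to chance imbalance and lost precision. Nor is the 0.023–0.039 peculiar to QALYs: all but the 0.009–0.011 reflects baseline differences persisting into follow-up, which would affect any unadjusted comparison of follow-up scores.

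**Conclusion.** The point holds in a limited form. Taken per visit, the pre-exercise QALY does not exist. Taken as one 0–6 month quantity, it has no before/after change, and a quarter of its weight is baseline health. With 15 per arm and no adjustment, a chance imbalance of one SE shifts the between-arm difference by 0.009–0.011 QALY through the baseline weight alone, or 0.023–0.039 in total, against 0.030 for a sustained gain of 0.08. These sizes rest on the assumed SD, correlation and gain; the 25% weight and the missing pre-programme interval follow from the schedule alone. The correction is worth making because quality of life is a stated objective and a listed critical metric. Conclusions on recruitment, retention, adherence and acceptability are unaffected.

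**What to change.** - For health-related quality of life, compare the EQ-5D-5L index between arms at 3 and 6 months, adjusted for the baseline index, with 95% confidence intervals.
- If QALYs are reported, calculate one per patient as the area under the index curve over 0–6 months. Compare arms only, adjusted for the baseline index.
- Remove the evaluation of QALYs before and after exercise.

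The cost is analysis wording only. All three assessments are already scheduled, so no visit, questionnaire or patient is added.

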##### Functional ability test

The functional ability will be assessed through a 6-minute walking test. Although this test lacks organ specificity in SSc, it can provide a valuable outcome parameter and, thus, is suggested as a regular assessment in this clinical condition [23]. Patients will be instructed to walk as far as possible back and forth on a 10 m corridor for 6 minutes. They will also be instructed to slow down, stop and/or rest as necessary if they experience breathlessness or become exhausted, but to resume walking as soon as they feel able to. The laps and the total walking distance will be recorded on a worksheet.

### Statistical analysis

The sample size for a feasibility study should be adequate to estimate the critical metrics needed to assess the feasibility of conducting the definitive study, with sufficient precision [34]. The critical metrics are the consent rate (i.e. the proportion of eligible patients who consent to participate and be randomised), improvement in microcirculation and quality of life as well as compliance with treatment, and attrition rates. Fifteen patients in each group (*n* = 30 in total) will provide a sufficiently precise (within 15 percentage points for a 90% confidence interval) estimate of the proportion willing to be randomised, assuming 35–40% intention to be randomised.

The SPSS software (version 23, IBM SPSS, New York, USA) will be used to enter quantitative data and cleaning the data and to carry out missing values imputation and statistical analysis. The descriptive statistics, including mean and standard deviation, will be presented for basic demographics and primary and secondary outcomes of the patients in intervention and control groups. For categorical data, the χ^2^ test will be used to infer on the significant association. Independent and paired samples *t* tests will be used to account for the changes upon the primary and secondary outcomes within the group at pre- and post-exercise intervention but also between the two groups. Kolmogorov–Smirnov and Shapiro–Wilk tests will be used to test the normal distribution of the dependent variable and Levene’s test will be used to test the homogeneity of variances. Pearson’s r will test any relations and interactions between our variables. The qualitative analysis will be performed using framework analysis [35], aiming to describe individuals’ experiences of exercise, searching for common, recurrent patterns but also exploring participant experiences that might explain behaviour and improve advice and services in the future. Data saturation will be achieved when similar themes arise repeatedly and no new themes arise in the interview.

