## Methods/Design

### Study design

The FESS (Feasibility of Exercise in Systemic Sclerosis patients) study is a mixed methods feasibility study involving a randomised controlled trial. Thirty patients with SSc receiving usual care (e.g. medical treatment) will be randomly assigned (via block randomisation remotely by the study chief investigator) to either an exercise group (12-week supervised exercise programme) or to a control group being in receipt only of the usual care. Patients will be followed for 6 months following randomisation (Fig. 1). It is not feasible to perform masking of patients or study investigators regarding the allocated treatments due to limited resources. The study is being run at Sheffield Hallam University in collaboration with the Royal Hallamshire Hospital (Sheffield Teaching Hospitals, NHS, UK). The study’s protocol and registration have been published in ClinicalTrials.gov (NCT number: NCT03058887).

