### Feasibility outcomes

The primary aim of this study is acceptability and feasibility of procedures for recruitment, allocation, measurement and retention as well as the adherence and enjoyment levels of the exercise programme. Recruitment rates will be assessed as the rate of invited patients who are eligible and consenting and will be reported in a CONSORT (Consolidated Standards of Reporting Trials) patient flowchart. Suitability of measurement procedures will be assessed via interviews and reasons for missing data. Reasons for dropouts will be used to evaluate the acceptability of allocation procedures and exercise programme. The acceptability of the exercise programme will also be assessed through questionnaires relevant to exercise task self-efficacy, intentions for engagement to exercise, enjoyment levels of exercise and the affect during exercise, and the physiological stress of exercise monitored by HR and RPE. The safety of exercise will be evaluated by the dropout number from the exercise group, and the number and type of adverse events.

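### The stated precision of the consent rate uses the 30 randomised patients as its denominator, although they are its numerator; the error is conservative and leaves n = 30 unchanged

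*Protocol article*

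**What the plan says.** The Statistical analysis section of the protocol article bases the sample size on precision, not power. It names the critical metrics as the consent rate, improvement in microcirculation and quality of life, compliance, and attrition. It defines the consent rate as "the proportion of eligible patients who consent to participate and be randomised".

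The next sentence gives the justification. Its subject is "Fifteen patients in each group (*n* = 30 in total"), and its claim is that this number "will provide a sufficiently precise (within 15 percentage points for a 90% confidence interval) estimate of the proportion willing to be randomised". The anticipated rate behind that claim stands in the closing clause of the sentence: "assuming 35–40% intention to be randomised".

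Two other places bear on who is counted:

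- Study design: "Thirty patients with SSc receiving usual care (e.g. medical treatment) will be randomly assigned". The abstract says the same. The 30 are randomised patients.
- Feasibility outcomes: "Recruitment rates will be assessed as the rate of invited patients who are eligible and consenting". Here the denominator is invited patients, a wider group than eligible patients.

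The article gives no other justification for n = 30, and no precision for any other critical metric.

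**The concern.** A proportion willing to be randomised has to be estimated in people who could still say no. Everyone among the 30 randomised patients has agreed, so within that group the proportion is 100% by construction. It cannot serve as the sample from which a rate of 35–40% is estimated.

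Three things are at stake, all modest.

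- The only sample-size justification in the article is wrong as written.
- The recruitment rate is a primary outcome and the first study objective, meant to inform a definitive trial, and its stated precision is not the precision the design would deliver.
- A reader of the paragraph does not learn how many eligible patients the trial has to reach in order to randomise 30. That matters for planning, because hospital recruitment comes from one rheumatology department, supplemented by self-referral.

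**Working it through.** **Inputs, all from the Statistical analysis section unless noted**

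- Precision target: "within 15 percentage points for a 90% confidence interval", so z = 1.645 and a half-width of 0.15.
- Anticipated proportion: p = 0.35 to 0.40.
- n = 30; the Study design section identifies these as randomised patients.
- Denominator by definition: eligible patients.

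**Step 1. Reproduce the stated figure.** Half-width h = 1.645 × √(p(1 − p)/n), with n = 30:

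- p = 0.35: 1.645 × √(0.2275/30) = 0.143, or 14.3 points
- p = 0.40: 1.645 × √(0.24/30) = 0.147, or 14.7 points

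This matches the stated 15 points. Solving for n at exactly 15 points gives 27.4 (p = 0.35) to 28.9 (p = 0.40), just under 30. Other readings with n = 30:

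| Method | Half-width, p = 0.35 to 0.40 (points) |
|---|---|
| Wilson, 90% | 13.8 to 14.1 |
| One-sided 90% | 11.2 to 11.5 |
| Continuity-corrected, 90% | 16.0 to 16.4 |
| Normal approximation, 95% | 17.1 to 17.5 |

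The figure is therefore a two-sided 90% interval with 30 as the denominator.

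**Step 2. Test that denominator.** If 30 were the number of eligible patients approached, the number randomised would be 30 × 0.35 = 10.5 to 30 × 0.40 = 12. That contradicts 15 per group.

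**Step 3. Use the denominator that the definition requires.** Eligible patients implied by 30 randomised:

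- p = 0.40: 30/0.40 = 75
- p = 0.35: 30/0.35 = 85.7, so 86

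Half-widths:

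- p = 0.40, n = 75: 1.645 × √(0.24/75) = 0.093, or 9.3 points
- p = 0.35, n = 86: 1.645 × √(0.2275/86) = 0.085, or 8.5 points

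**Step 4. Check against the way recruitment would stop.** If recruitment runs until 30 are randomised, the number of eligible patients is random and the standard error is p√((1 − p)/30). Then 1.645 × 0.40 × √(0.60/30) = 9.3 points and 1.645 × 0.35 × √(0.65/30) = 8.5 points, the same as in step 3. Exact 90% intervals are 30.5% to 50.2% for 30/75 and 26.4% to 44.2% for 30/86.

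**Step 5. The other proportions.** The article claims no precision for these and gives no anticipated rates, so the rates below are illustrative assumptions.

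- Attrition pooled over both arms, where 30 is the right denominator: 12.0 points at 20%, and at most 1.645 × √(0.25/30) = 15.0 points, at 50%.
- Compliance as a yes/no per patient in the 15 exercise patients: 12.7 points at 90%, 17.0 at 80%, 19.5 at 70% and 21.2 at 50%. The normal approximation is poor at this size: the exact 90% interval for 12 of 15 is 56.0% to 94.3%, which reaches 24 points below the estimate of 80%.

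**The case against.** The strongest reply is that nothing of consequence turns on the slip. The claim is an upper bound, and about 9 points is still within 15, so the trial does better on the consent rate than it promised. The number of patients, the design and the analysis stay as they are. All of that stands, and it is why this is a correction to a stated figure and not a flaw in the design. It does not rescue the sentence, which ties the precision to a group in which the rate cannot be estimated.

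A reader might infer that the justification fails for every critical metric. The article does not support that. The 15-point figure is claimed only for willingness to be randomised. For pooled attrition, 30 is the correct denominator and the half-width is about 15 points at worst. Microcirculation and quality of life are not yes/no rates, so a precision in percentage points has no direct meaning for them.

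A reader might also infer that the article promises 15 points for exercise compliance and misses it. It does not: compliance is listed in the preceding sentence, with no precision attached. Nor does the article define compliance as a yes/no per patient. If it is analysed as sessions attended out of 24, the half-widths for 15 patients in step 5 do not apply. Leaving those precisions to a fuller document is normal for an article.

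Finally, 75 to 86 is not the number to invite. Feasibility outcomes counts invited patients, some of whom will prove ineligible, and the recruitment section also admits self-referred patients, for whom the number who saw the announcement is unknown.

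**Conclusion.** The point holds as a correction of one stated figure. The precision of the consent rate was calculated on the 30 randomised patients, while the article's own definition requires eligible patients. The half-width should be about 8.5 to 9.3 points on about 75 to 86 eligible patients, against the stated 15.

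This rests on the article's 35–40% willingness, on all 30 patients being randomised, and on every eligible patient approached being counted. If willingness falls outside that range, the number of eligible patients and the half-width both shift. The separate caution, that the 15-point figure should not be read across to exercise compliance, is conditional on how compliance is defined and on assumed rates.

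**What to change.** Keep n = 30 and replace the precision sentence with wording such as:

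> *Randomising 30 patients at 35–40% willingness implies about 75–86 eligible patients approached, and a larger number invited, giving a 90% confidence interval of about 9 percentage points either side for the consent rate.*

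Say beside it which denominator, eligible or invited, each reported recruitment proportion uses, since the Statistical analysis and Feasibility outcomes sections differ.

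Do not word the paragraph so that the consent-rate precision appears to cover compliance. If compliance is to be analysed as a per-patient proportion, a note could say that with 15 exercise patients the half-width would be about 13 to 21 points for assumed rates from 90% down to 50%, that this is a normal approximation, and that exact intervals are wider. These rates should be marked as illustrative, because the article gives none.

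The cost is a sentence or two of wording, with no extra patients and no change to design or analysis. It does require a log of eligible patients approached, which the planned CONSORT flowchart should already call for.

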## Background

Systemic sclerosis (SSc) is an autoimmune connective tissue disease characterised by tissue fibrosis and vascular involvement. Vasculopathy is directly implicated in the pathogenesis of SSc representing acute manifestations (e.g. pulmonary arterial hypertension, digital ulcers). Raynaud’s phenomenon (RP) is one of the first clinical manifestations presented in SSc, with a 95% prevalence across patients. RP precedes any other clinical symptoms of SSc and is due to hypoxia in the extremities in response to cold. Evidence suggests that endothelial injuries in conjunction with an imbalance in the vascular tone trigger RP [1], which in turn develops digital ischemia, a serious complication for patients with SSc. Morbidity rates in patients with SSc due to digital ischemia reach approximately 30% annually [2]. Patients with chronic digital ulcers develop irreversible tissue loss [2], which usually requires hospitalisation for iloprost infusion [3] lasting from 5 days to 3 weeks. Hospitalisation is a psychologically stressful procedure for the patient, directly affecting their health-related quality of life (HRQoL). The most common side effects of iloprost infusion are headache, flushing of the skin, nausea, vomiting and sweating. Amputation has been reported to occur in one or more digits due to ischemia in 20.4% of patients with SSc, 9.2% of which have multiple digit loss [4].

A recent review paper has aggregated the studies that have examined the effects of exercise in SSc patients with and without pulmonary involvement [5], summarising the beneficial effects, including good exercise tolerance and increased aerobic capacity [6–8], muscle strength [6, 9], hand mobility, [10–12], functional ability in daily activities [11] and increased HRQoL [10, 11]. However, most studies lacked reporting of the intensity of their exercise programme and none examined the effects of exercise on the vasculature. Therefore, it is important to explore the feasibility of a training protocol that would be able to (1) improve vascular function and potentially decrease the frequency and severity of digital ischemia and ulcers, and (2) have the potential to decrease the use of pharmacological agents. These agents are used to improve microcirculation with short-term (e.g. oedema, headaches, heart palpitations, dizziness and constipation) and long-term (e.g. heart dysfunction, increased cardiovascular risk) side effects and financial cost implications.

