## Discussion

Digital ischemia is a direct result of RP in SSc patients that adversely affects their HRQoL. The number of incidents that require hospitalisation and, occasionally, digital amputation is not negligible (30%) [2]. There is strong evidence from a wide range of clinical conditions in which vascular disease plays a leading role in their pathophysiology, that exercise, and more specifically HIIT and RT, are able to improve the endothelial vascular function and, thus, to increase macro- and microcirculation. Based on that evidence, we will attempt to implement a combined exercise protocol, primarily assessing its feasibility and, secondarily, its efficacy on vascular tone. The feasibility study will provide important evidence about the effectiveness of supervised exercise training as a complementary treatment to the usual care (e.g. medical treatment) for improving microcirculation in the digital area, physical fitness, functional ability and HRQoL in SSc patients. The findings will inform a future definitive multicenter randomised controlled trial with a larger sample size. We acknowledge that our sample size might be a limitation for the current study but we need to stress that FESS is a feasibility study in a novel area and we will strictly adhere to the pre-defined eligibility criteria to present a consistent and reproducible outcome. Moreover, the ratio between women and men is uneven; however, the women to men ratio in those with SSc is estimated to 5.2:1 in northeast England [36]. Overall, the study is expected to provide valuable evidence for future research with SSc patients.

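### Secondary outcomes: within-arm paired t tests do not estimate the exercise effect, and the between-arm t test, though valid, leaves the baseline value unused as a covariate

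*Protocol article*

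**What the plan says.** The Statistical analysis section of the protocol article names independent and paired samples t tests in one sentence: "tests will be used to account for the changes upon the primary and secondary outcomes within the group at pre- and post-exercise intervention", which continues "but also between the two groups". So both a within-arm and a between-arm test are planned. No covariate or regression model is named. The section does not say whether the independent test is applied to follow-up values or to change, nor which of the tests is to be read as the effect of exercise.

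The data for a better analysis are already planned. Study design describes a randomised usual-care control group. Outcome measures sets the assessments at baseline, 3 months and 6 months. Baseline measurements lists microvascular function, arm-crank peak oxygen uptake, the 6-minute walk and the EQ-5D-5L.

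The secondary outcomes are meant to carry weight. Statistical analysis counts improvement in microcirculation and quality of life among the critical metrics. The Abstract says the data will be used to establish what exercise does to the microvasculature. The Discussion says the study "will provide important evidence about the effectiveness of supervised exercise training".

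**The concern.** A significant pre-post change in the exercise arm shows that those patients changed, not that exercise changed them. Anything that moves both arms can make it significant. The protocol gives some grounds for expecting such movement. Raynaud's phenomenon "is due to hypoxia in the extremities in response to cold" (Background), and the visits are months apart. Baseline testing takes place at the same first visit as habituation (Recruitment of participants). Patients and investigators are not masked (Study design).

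The sentence lists within-arm and between-arm tests side by side with no order of priority. A reader of the results could therefore take a significant paired test in one arm and a non-significant one in the other as evidence for exercise, and carry that pre-post change into the planning of the definitive trial. Separately, with 15 patients per arm, a between-arm test without the baseline covariate gives up precision that the collected data could supply.

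**Working it through.** **Inputs from the protocol.** "Fifteen patients in each group"; paired and independent t tests; outcomes at baseline, 3 and 6 months. No effect size, SD, significance level or power is given for any secondary outcome.

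**The plan's own figure.** The only quantitative design figure is the precision of the proportion willing to be randomised: "within 15 percentage points for a 90% confidence interval", "assuming 35–40% intention to be randomised". The half-width is 1.645 × √(p(1−p)/30), which is 14.3 points at p = 0.35 and 14.7 points at p = 0.40. It reproduces, but it concerns consent and has no bearing on the secondary outcomes.

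**Assumptions.** The documents give no values, so ranges are used: baseline/follow-up correlation ρ of 0.3, 0.5, 0.7 and 0.8; a change common to both arms of 0, 0.25 or 0.5 SD of the outcome; normal data with equal SDs; two-sided 5% tests; 40,000 simulated trials per setting with 15 per arm.

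**Step 1: within-arm tests when exercise has no effect.** The SD of change is √(2(1−ρ)) outcome SDs, so a given common change is easier to detect as ρ rises.

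| ρ | Common change | Exercise arm significantly improved | Exercise significant, control not |
|---|---|---|---|
| 0.3 | 0.25 SD | 11.5% | 10.1% |
| 0.5 | 0.25 SD | 14.2% | 12.1% |
| 0.7 | 0.25 SD | 21.0% | 16.7% |
| 0.8 | 0.25 SD | 30.1% | 21.3% |
| 0.3 | 0.5 SD | 33.5% | 22.6% |
| 0.5 | 0.5 SD | 43.8% | 24.8% |
| 0.7 | 0.5 SD | 64.2% | 23.1% |
| 0.8 | 0.5 SD | 81.3% | 15.2% |

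The last column is close to P(1−P), where P is the column before it. At ρ = 0.5 and 0.5 SD, 0.438 × 0.562 = 0.246. With no common change, the exercise arm is significantly improved in about 2.5% of trials.

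**Step 2: between-arm tests in the same settings.** The t test on follow-up values, the t test on change and ANCOVA all reject in 4.8% to 5.1% of trials. All three are valid.

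**Step 3: precision.** Relative to the outcome variance, the variance factors are 1 for a t test on follow-up values, 2(1−ρ) for a t test on change, and 1−ρ² for ANCOVA. The ratio of ANCOVA to change is (1+ρ)/2. The number of patients that each t test needs to match ANCOVA with 30 is 30/(1−ρ²) for follow-up values and 60(1−ρ)/(1−ρ²) for change. Power is simulated for an illustrative true effect of 0.8 SD.

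| ρ | ANCOVA ÷ change | ANCOVA ÷ follow-up | Patients to match: change | Patients to match: follow-up | Power: ANCOVA / change / follow-up |
|---|---|---|---|---|---|
| 0.3 | 0.65 | 0.91 | 46 | 33 | 58% / 43% / 56% |
| 0.5 | 0.75 | 0.75 | 40 | 40 | 67% / 56% / 56% |
| 0.7 | 0.85 | 0.51 | 35 | 59 | 82% / 78% / 56% |
| 0.8 | 0.90 | 0.36 | 33 | 83 | 93% / 92% / 56% |

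ANCOVA is the most precise of the three at every ρ shown. The gain is small against change at high ρ and small against follow-up values at low ρ.

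**The case against.** The strongest reply is that a randomised comparison is planned in the same sentence, that it is valid, and that nothing says a within-arm result will be called the exercise effect. This is correct and limits the point. A reader might infer that the between-arm t tests also generate false effects. They do not: they hold about 5% in every null setting, and any drift shared by both arms cancels in them.

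The size of a common change is assumed, and the protocol takes steps against it. Habituation is described before the baseline assessments, and microvascular testing is done in a room at 22–24 °C (Iontophoresis). These steps reduce the risk without removing it: they do not control season for symptoms or quality of life, nor the effect of knowing the allocation.

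Three further stronger readings are also unsupported:

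- At ρ = 0.5 and a 0.5 SD common change, exactly one arm is significant in 49% of trials. That counts both directions; the pattern that flatters exercise is about half, 25%.
- The choice of test does not distort the SDs passed to the definitive trial. Means and SDs are to be reported by group, and these do not depend on which test is run.
- The EQ-5D-5L questionnaire section says "To evaluate the EQ-5D-5L outcome in the overall pre- and post-exercise intervention we will calculate the quality-adjusted life years". The wording is loose, since QALYs accrue over follow-up, but how they are computed and adjusted is detail that an article may leave to an analysis plan.

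Finally, these are secondary outcomes of a feasibility trial whose primary outcomes are recruitment, retention, acceptability and adherence. That lowers the priority. It does not answer the point, because the protocol itself proposes to draw conclusions on effect from these outcomes.

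**Conclusion.** The point holds as a recommended improvement, not as an error that invalidates the plan. The within-arm paired tests do not estimate the randomised effect. With no true effect and a common improvement of 0.25 to 0.5 SD, the exercise-arm test is significant in about 12% to 81% of trials, and the misleading contrast between arms arises in about 10% to 25%. The unadjusted between-arm test is sound but less precise. If it is done on change, which the word changes in the sentence favours, ANCOVA reduces the variance by 10% to 35%; if on follow-up values, by 9% to 64%. The common change and the correlation (0.3 to 0.8) are assumptions, since the protocol gives neither. If no common change occurs, the false-effect risk in the exercise arm falls to about 2.5% and only the precision argument remains.

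**What to change.** Replace the t-test sentence, for the continuous secondary outcomes, with wording such as:

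> Each continuous secondary outcome, including the EQ-5D-5L index, will be compared between arms as randomised at 3 and 6 months by ANCOVA, or by one mixed model covering both visits, adjusting for the baseline value of that outcome. The adjusted mean difference with its 95% CI will be reported as the estimated effect of exercise. Within-arm changes will be described and not tested.

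The cost is one degree of freedom per model and a change of wording. No new data, visits or patients are needed, and the SPSS software already named in the protocol can fit these models. The change should be made before the outcome data are analysed.
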